### Administration of the trial medication

The intervention drugs will be packaged in capped plastic containers each containing 50 capsules (42 + 8 extra capsules). Treatment will be initiated in hospital and continued at home. The first dose will be administered under direct observation at the clinic. Participants and their caretakers will then be carefully instructed about taking subsequent doses before they return home. Each participant will be visited at home at 2, 4 and 6 weeks for adherence and safety monitoring (detailed below). Parents/carers will be reminded weekly through mobile phone contact to ensure the participants take the assigned interventions.

The product will be taken with water between 6.00–9.00 am and at about the same time each day. Should a carer forget to give the dose at the set time, they will be advised to give it as soon as this is realised and to continue the recommended regimen until the dose is completed. Participants will be observed for at least 30 min after taking the medication. Should they vomit within 30 min of receiving the intervention drug, the full dose will be re-administered. Such vomiting will be documented. On a single day, repeat dosing will be attempted once. The eight additional capsules in each pack are to cater for such eventualities.

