### Follow period and study outcome determination

Study participants will be re-evaluated at 6, 12, 18 and 24 months. Only clinical assessments will be performed at 6, 12 and 18 months. At 24 months, however, participants will again be hospitalised for one week for inpatient observation and testing, during which all the pre-randomisation procedures and tests will be repeated to determine study outcomes.

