### Assessment of efficacy and safety

#### Primary efficacy outcome

The objective of the trial is to determine if targeting *O.volvulus* through drugs which kill *Wolbachia* can modify the pathogenic processes in nodding syndrome. We will therefore investigate the effects of doxycycline compared to placebo on the presence and titres of serum antibodies to HNPs (identified in the concurrent case-control study) or leiomodin and on inflammatory markers, the microfilaria density and *Wolbachia* load. The primary efficacy measure will be the proportion patients testing positive for and levels or titres of antibodies to HNPs or leiomodin at 24 months.

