### Interim analyses and criteria for termination of the trial

An interim analysis is planned for when a total of 132 participants have completed the 24-month assessment. This number will be sufficient to demonstrate a 50% reduction in the proportion of participants testing positive for antibodies to HNPs at 24 months compared to baseline at β = 0.80 and α = 0.05. This information will be reviewed by an independent Data and Safety Monitoring Committee (composed of an experienced epidemiologist who will chair the committee, a paediatric neurologist and a general paediatrician) which may recommend stopping the trial on safety rules or efficacy reasons. The Peto-Haybittle rule will be used to stop the trial for efficacy reasons: i.e. to consider stopping the trial early because of efficacy, a *p-value* < 0.001 should be achieved at the interim analysis. Accordingly, the early stopping rules will be: (1) proof beyond reasonable doubt of a difference in primary outcome between the study and control groups and (2) evidence that would substantially alter the choice of treatment for patients. Otherwise, the overall significance level of the final analysis will be *p* < 0.05. *However, in order not to miss an early but clinically relevant improvement in secondary outcomes and in particular, seizure control, Makerere University School of Medicine Research and Ethics Committee recommended that the first interim analysis should be conducted when 132 participants complete the 12-month assessment. If significant differences fulfilling the Peto-Haybittle rule are observed at this stage, the trial may be stopped.*

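### The 12-month interim look permits an efficacy stop that the primary-outcome stopping rule cannot support, on an outcome that is not fixed and with no stated fate for 24-month antibody follow-up

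*Protocol article*

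**What the plan says.** All references are to the protocol article.

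- **Primary efficacy outcome.** The measure is the proportion positive for, and the "levels or titres of antibodies to HNPs or leiomodin at 24 months".
- **Follow period and study outcome determination.** "Only clinical assessments will be performed at 6, 12 and 18 months". At 24 months participants are readmitted for a week, "during which all the pre-randomisation procedures and tests will be repeated to determine study outcomes".
- **Interim analyses and criteria for termination of the trial, first part.** "An interim analysis is planned for when a total of 132 participants have completed the 24-month assessment". The number is justified by a halving of antibody positivity at 24 months. The efficacy boundary is p < 0.001. The first of the two early stopping rules is "proof beyond reasonable doubt of a difference in primary outcome between the study and control groups"; the second is evidence that would change the choice of treatment.
- **Same section, closing sentences.** On the recommendation of an ethics committee, and so that an early gain in secondary outcomes (seizure control in particular) is not missed, "the first interim analysis should be conducted when 132 participants complete the 12-month assessment". Then: "If significant differences fulfilling the Peto-Haybittle rule are observed at this stage, the trial may be stopped".

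The closing sentences name no single outcome for the stop. They do not say how it relates to the first stopping rule, or whether participants would still attend the 24-month visit afterwards.

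**The concern.** The stopping criteria require a primary-outcome difference. The first look at which stopping is allowed uses a visit where that outcome is not scheduled. A monitoring committee that applied the section literally could not use 12-month visit data to satisfy the first rule, yet the last sentence tells it that the trial may be stopped.

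Two gaps make this worse. Seizure control is given only as the leading example of the secondary outcomes, and the protocol expresses it in more than one way: a proportion seizure-free under the secondary efficacy outcomes, and a time to seizure resolution under the statistical analysis. The committee therefore has no single test to hold against p < 0.001. The number 132 was also chosen for the antibody comparison and says nothing about what the look can detect on seizures.

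What is at stake is the primary endpoint. It needs a sample at 24 months from each participant. If a stop at the 12-month look were taken to end follow-up, most or all of those samples would not exist.

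**Working it through.** **Step 1. Where 132 comes from.** Inputs from the sample size and interim sections: 50% positive on placebo, a 50% reduction (to 25%), 80% power, 5% significance (taken as two-sided). Mean proportion = 0.375, difference d = 0.25.

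n per arm = [1.96·√(2·0.375·0.625) + 0.8416·√(0.5·0.5 + 0.25·0.75)]² / d² = (1.3419 + 0.5567)² / 0.0625 = 57.7, so 58.

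With continuity correction: (57.7/4)·[1 + √(1 + 4/(57.7·0.25))]² = 65.4, so 66 per arm, **132 in total**. This is an exact match.

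The same method reproduces the full sample. For 50% against 30% it gives 103 per arm, and 103/0.90 = 114.4, so 115 per arm and **230 in total**.

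So 132 is the size of a 24-month antibody comparison. It reappears unchanged as the trigger of the 12-month look, and no event rate, effect or power is given for any seizure outcome there.

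**Step 2. The two looks side by side.**

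| | Look at 24 months | Look at 12 months |
|---|---|---|
| Trigger | 132 complete 24 months | 132 complete 12 months |
| Antibody result scheduled at that visit | Yes | No |
| Can the visit data meet the first stopping rule? | Yes | No |
| Outcome for p < 0.001 | Primary outcome | Not fixed; secondary outcomes, seizure control in particular |
| Stated basis for 132 | Antibody positivity, 50% to 25% | None |

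The abstract says that study outcomes are assessed at 6, 12, 18 and 24 months. The follow-up section limits the first three of these visits to clinical assessments, so the abstract does not resolve the conflict.

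**Step 3. How many would have a 24-month result at the 12-month look.** The accrual period A (months) is not given, so it is varied. Assume uniform accrual of 230 and, first, no dropout.

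- The 132nd participant enters at (132/230)·A, so the look falls at (132/230)·A + 12.
- Those with 24-month data entered by (132/230)·A − 12. Their number is 230·[(132/230)·A − 12]/A = 132 − 2760/A, or zero if this is negative.
- Randomised by the look: 132 + 2760/A, capped at 230.

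| A (months) | With 24-month data | Randomised by the look |
|---|---|---|
| up to 20.9 (= 2760/132) | 0 | 230 |
| 24 | 132 − 115 = 17 | 230 |
| 36 | 132 − 76.7 = about 55 | about 209 |
| 48 | 132 − 57.5 = about 75 | about 190 |

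**Step 4. Sensitivity to dropout.** The trigger counts completers. If the whole 10% loss in the sample size section had occurred by 12 months, about 132/0.9 = 147 would have to be enrolled. The zero threshold becomes 2760/147 = about 19 months. At A = 36, about 147 − 77 = 70 would have reached 24 months, about 63 of them with data. The conclusion does not change.

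**Step 5. Type I error.** A single look at p < 0.001 on the primary endpoint, at information fraction 132/207 and with the final test at 0.05, gives an overall two-sided error of about 0.0501. The boundary itself is not the problem.

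**The case against.** The strongest reply is that the closing sentences are a declared exception. They are set against the general rules, give a reason, and name the body that asked for the look. On that reading the section relaxes its first rule for one look and does not contradict it by oversight. This is a fair reading, but the text never says that the first rule is suspended there, nor what replaces it.

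A reader might infer more than the document supports:

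- **That a stop would leave the antibody question unanswered.** The wording is permissive, the committee only recommends, and nothing says that 24-month sampling would end. The loss in Step 3 is conditional on that.
- **That any secondary outcome could easily stop the trial by chance.** Seizure control is singled out, and laboratory outcomes are not scheduled at 12 months. Even with ten independent null outcomes, the chance that one crosses p < 0.001 is 1 − 0.999¹⁰, about 1%.
- **That everyone would already have been treated, so a stop would achieve nothing.** Treatment lasts six weeks, but this depends on A. At A = 48, about 40 of 230 would not yet be randomised. An efficacy stop also serves to act on benefit, including for placebo participants, which the second stopping rule reflects.
- **That the 24-month look has the same fault.** It does not: the primary outcome exists there and the first rule can operate.

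What happens to follow-up after a stop is often left to the full protocol or a committee charter. That weakens any complaint of omission. It does not remove the mismatch between the stopping rule and the visit schedule, both of which this document fixes.

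**Conclusion.** The point stands in this form. Data from the 12-month visit cannot meet the first stopping rule, the outcome that may trigger a stop at that look is not fixed, and 132 has no stated power basis there. These three statements follow from the text without further assumption.

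The possible loss is conditional. If a stop ended follow-up, the primary endpoint would be missing for most or all participants: all of them for an accrual period up to about 21 months, and all but about 55 of 230 at 36 months. This assumes uniform accrual and no dropout, and the accrual period is not given. The section should be corrected, because as written it permits a stop before the primary endpoint exists and does not protect the collection of that endpoint.

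**What to change.** Reconcile the interim section with the follow-up schedule:

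1. Name the single seizure outcome, with its definition and time point, to which p < 0.001 applies at the 12-month look.
2. State that the primary-outcome stopping rule applies only to the look at which the primary outcome exists.
3. State that crossing the 12-month boundary leads to a committee recommendation and possible early reporting of that outcome, while all randomised participants are still followed to the planned 24-month visit with antibody testing and the primary analysis is done.
4. Remove the 132 power justification from the 12-month look. The number may stay as a trigger, provided it is not presented as powered for seizures.

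No change to the 24-month look is needed. The cost is a protocol clarification and notification of the ethics committee that asked for the early look. The 24-month visit is already in the schedule, so no new assessment is added.

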## Discussion

The goal of this study is to understand the pathogenesis of, and to develop specific interventions for, nodding syndrome. Currently, there is no specific treatment for nodding syndrome. The only available treatment is a package of therapies aimed at symptomatic relief [32]. This project has the potential to advance the understanding of nodding syndrome, allow definitive diagnosis and gain insight into potential new approaches for treatment and prevention. If evidence of neuro-inflammation is found and/or specific autoantibodies, immune-modulatory therapies, for example with high dose steroids, may be considered at symptom-onset [2]. In addition, a biologic association between nodding syndrome and *O.volvulus* would allow escalation of treatments and prevention. If a potential use for doxycycline, as treatment for nodding syndrome is observed, it would also be a proof of principle that treatment is possible in older children. Such a strategy could also be explored for younger newly affected children. It is important to point out that the proposed use of doxycycline is based on its effectiveness as treatment for adult *O. volvulus.* Its success will not depend on *Wolbachia* playing a direct role in the pathogenesis of NS (although it may), rather, it is a test of the broader hypothesis that *O.volvulus* plays a role in the pathogenesis of NS.

The approach of using doxycycline is supported by the facts that (1) *O.volvulus* infection has had the most consistent association with nodding syndrome out of many potential risk factors examined to date [33]; (2) doxycycline is a cheap and safe drug and the only curative treatment for adult *O.volvulus* currently available [23]; (3) a direct intervention has considerable advantages over epidemiological association studies in elucidating causality. This is thus a low risk but potentially high gain approach: a positive result would have great significance in understanding both pathogenesis and offering a hope of treatment, whilst a negative result would still be helpful in indicating that whatever the pathogenesis, a simple approach to reducing *O.volvulus* load may not necessarily offer an advantage.

The trial has as one of its major strengths - the dual benefit of potentially determining both the pathogenesis of nodding syndrome and providing a specific treatment intervention. This is supported by the use of both clinical and laboratory biomarkers either as primary or secondary outcome measures. The main weakness is that with the decline in incident cases who would potentially register most improvements with treatment, the study will have to rely on patients with established symptoms in whom, probably lower degrees of improvements will be observed.

## Abbreviations

AE: Adverse event
AMPA: α-amino-3-hydroxy-5-methyl-4-isoxazolepropionic acid
CASPR-2: Contactin-associated protein-like-2
CRF: Case Report form
DSMB: Data and safety monitoring board
GABA: Gamma amino-butyric acid
GCP: Good Clinical Practice
HIV: Human Immuno-deficiency virus
IB: Investigator’s Brochure
ICH: The International Conference on Harmonisation
IEC/IRB: Independent Ethics Committee / Institutional Review Board
IMP: Investigational Medicinal Product
ITT: Intention to treat
NMDA: N-methyl-D-aspartate
NS: Nodding syndrome
NSPs: Neuron surface proteins
PK: Pharmacokinetic
RBC: Red Blood Cells
SAE: Serious Adverse Event
SAE: Severe adverse event
SD: standard deviation
SOP: standard operating procedure
SSA: Sub-Saharan Africa
SUSAR: Serious unexpected adverse event or reaction
VGKC: Voltage Gated Potassium Channel Protein Complex
WHO: World Health Organisation
